#### Randomization

To help ensure comparability of the participants conducting the programme and the seniors in the control group, we looked for the best possible match with respect to sex, age, intellectual disability, the use of a walking aid and provider service. The matching procedure was conducted with the data of the potential 237 participants (see previous Paragraph) using chi-square and t-tests. The best match was found when the ten day-activity centers were divided into two specific groups of five centres each. We subsequently checked the comparability of important day-activity centres’ characteristics in both groups, that is the availability of a gymnasium nearby and involvement of a physical-activity instructor in the day-activity centres’ activities. These characteristics appeared to be comparable. The chairman of the steering group, in presence of the researcher and a senior staff member Public Relations, randomly selected one of the two groups of five day-activity centers who will conduct the programme. The remaining group of five day-activity centres will serve as the control group. Because the implementation of the programme has to be prepared and organized, the sequence is only concealed for the clients and family, not to the day-activity centres’ managers. After the informed consent procedure has ended, all participants and/or their family will receive a confirmation of participation in the study and information about the intervention allocation.

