Seniors had to be aged 45 years and over and to be able to participate in groups. Clients who were dependent on a wheelchair inside, who had dementia or had a medical contra-indication for participating in the physical activity programme would be excluded from the study. Managers of the selected ten day-activity centers provided anonymous information about their clients on date of birth, gender, level of intellectual disability, use of walking aid, presence of dementia and the ability to participate in group activities. Clients who satisfied the inclusion criteria are selected (n = 237). Clients who are competent according to their behavioral therapist, will be informed about the project by the staff members who are familiar to them. The information will be structured using specific Patient Information Forms and subsequently written informed consent will be obtained. If older adults are not sufficiently competent to give informed consent themselves, Patient Information Forms and informed consent forms will be sent by mail to their legal representatives. Informed consent for blood sampling will be obtained separately and is no precondition for participation.

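### Managers know the allocation during recruitment, and participants are told their arm when consent closes rather than after baseline, so the sample and the baseline used for adjustment are open to bias

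*Protocol article*

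**What the plan says.** The Randomization section reports the draw as already done: the chairman of the steering group "randomly selected one of the two groups of five day-activity centers who will conduct the programme". It then states who is kept unaware: "the sequence is only concealed for the clients and family, not to the day-activity centres’ managers". The reason given is that the programme must be prepared in the centres.

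Consent is described in the future tense, under Selection of day-activity centres and participants. Clients judged competent "will be informed about the project by the staff members who are familiar to them", with written information forms as support. For the others, "Patient Information Forms and informed consent forms will be sent by mail to their legal representatives". The same section says that clients who "had a medical contra-indication for participating in the physical activity programme would be excluded from the study", and it also excludes those dependent on a wheelchair indoors. The data that managers supplied to form the list of 237 were date of birth, gender, level of disability, walking aid, dementia and ability to take part in groups.

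The point at which participants learn their arm is fixed in Randomization: once consent has closed, "all participants and/or their family will receive a confirmation of participation in the study and information about the intervention allocation". The evaluation step (under Monitoring execution of the programme) says that outcomes are measured at baseline and at eight months, and that steps come from a pedometer worn for at least 4 days. It does not place baseline before or after the message. The Analysis section compares end-of-intervention outcomes adjusted for baseline.

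**The concern.** In a cluster trial where individuals are recruited after the clusters are allocated, randomization protects the comparison only as far as entry does not depend on the arm. Here two routes to dependence are open.

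- **Entry.** People connected with the centres know the arm while consent is sought and possibly while the last exclusions are applied. A contra-indication is defined against taking part in a programme that only five of the ten centres will run, so it may be looked for less evenly in the other five. If frailer seniors were filtered out more in intervention centres, the arms would differ for reasons other than the programme.
- **Baseline.** A pedometer count is behaviour, and it can change when people know they are about to join, or not join, an activity programme. If disclosure precedes the baseline count, the covariate may itself be affected by allocation, and adjusting for it then moves the effect estimate.

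**Working it through.** The article gives no figure for this point, so the first check is the order of events.

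| Step | Where | Placed relative to the draw |
|---|---|---|
| Manager data, list of 237, matching | Selection; Randomization | Before |
| Draw of one group of five centres | Randomization | – |
| Consent by familiar staff or by mail | Selection | After (future tense; managers already know) |
| Contra-indication and wheelchair exclusions | Selection | Not stated; not among the listed manager data |
| Participants told their arm | Randomization | After consent ends |
| Baseline pedometer measurement | Evaluation step | Not stated relative to disclosure |

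Two steps have no fixed place, and the only stated trigger for disclosure is the close of consent.

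**Share of the pool decided after the draw.** The article expects about 50% consent: 0.50 × 237 = 118.5, so about 118 enter. The arms were matched on all 237. Roughly half of those people leave the comparison after managers know the arm.

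**Scale of a disturbed baseline (illustration).** The baseline-adjusted effect is (Y_I − Y_C) − b(X_I − X_C), where Y is mean steps at eight months, X is mean baseline steps and b is the baseline slope. If knowing the arm shifts X_I by d, while Y, X_C and b stay the same, the effect changes by −b × d.

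Assumed, not in the article: b = 0.6 and d = 100 to 500 steps. From the article: target difference 1073 steps.

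- d = +100: −0.6 × 100 = −60 steps; 60/1073 = 6%.
- d = +500: −0.6 × 500 = −300 steps; 300/1073 = 28%.
- With d negative the sign reverses and the effect is overstated by the same amounts.

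Other assumed inputs give a similar order: b from 0.5 to 0.8 and d from 200 to 500 give 0.5 × 200 = 100 to 0.8 × 500 = 400 steps, or 9% to 37% of 1073.

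**Scale of differential recruitment (illustration).** Suppose that in one arm only, willingness to consent correlates r with steps, under a normal model with 50% consent. Mean steps among consenters then shift by r × 0.399/0.5 × SD. With the article's SD of 2146, r = 0.1, 0.2 and 0.3 (assumed) give 171, 342 and 514 steps. These are imbalances before adjustment. An undisturbed baseline would absorb the part it reflects, but selection on unmeasured factors would remain.

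**The case against.** The case on the other side has real substance. Clients and family, who take the consent decision, are concealed until consent ends. Mailed consent to legal representatives is less exposed to centre staff. Competence is judged by a behavioural therapist, and the information is structured by forms. The main eligibility list preceded the draw. Managers' knowledge has a stated practical reason. A journal article may also leave the calendar of letters and measurements to a fuller protocol.

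A reader might infer four stronger things, which the article does not support:

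- **That baseline is measured after disclosure.** No section says so. The order is left open.
- **That the staff who inform clients know the allocation.** Only managers are named as unconcealed. Managers and centre staff do sit together on the project group (Forums for implementation), and staff in the intervention centres are trained for the programme (Materials and training), so their knowing is plausible but not stated.
- **That the two exclusions must come after the draw.** They are missing from the listed manager data, which suggests later application, but their timing is not given. As written they apply to the whole study, so uneven use is a risk and not a fact.
- **That no model could repair the baseline problem.** Comparing eight-month steps without the baseline covariate does not use the disturbed value. That would not mend differential entry.

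The stated trigger survives the objection. The article does more than stay silent on the calendar: it ties disclosure to the end of consent, an event that does not protect the baseline. The safeguards reduce the recruitment risk, but none covers people who know the arm and may influence who is approached or excluded.

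**Conclusion.** The concern holds as a risk that the described sequence leaves open, not as bias shown to exist. What is stated outright is that allocation precedes consent, managers know it during recruitment, familiar staff inform competent clients, and participants learn their arm when consent closes. Late exclusions, and baseline falling after disclosure, are possibilities that nothing in the article rules out.

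The understatement of 60 to 300 steps if the intervention-arm baseline is raised, and the equal overstatement if it is lowered, rest wholly on the assumed shift and slope and on a shift that does not carry through to eight months. The likely direction cannot be settled from the article, and neither can the size of any differential recruitment. The point merits a change because the remedy is cheap, not because the size is established.

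**What to change.** 1. In Randomization, change the trigger for telling participants their arm from the end of consent to completion of that centre's baseline measurements, including the pedometer days.
2. Until then, restrict knowledge of the allocation to the managers who must prepare, and have client-facing staff in all ten centres use the same information script.
3. Apply the existing exclusion criteria, unchanged, with one checklist in all ten centres before disclosure, and state when this is done. Keep everyone who passes in the analysis.
4. As a supporting check, compare consenters with non-consenters by arm on the list data already held: age, sex, level of disability and walking aid.

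The cost is a somewhat later letter and preparation in the intervention centres sequenced around baseline, which needs care because preparation is the reason managers are told. The check in item 4 needs no new data beyond a record of who consented. It describes differential entry on the listed items and cannot exclude it on others.

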#### Forums for implementation

Several forums are formed for the purpose of optimal motivation and support. Managers of the three ID care provider services regularly met with the research group to discuss the preconditions for implementation of the programme. Client boards were informed at the beginning of the study. A central *project group* is formed at the beginning of the study, to advise the researchers during every step of implementation of the programme. The project group consists of day-activity centres’ managers and day-activity centre’s staff, movement experts and a behavioural therapist. During the programme’s development phase, we already examined the potential fit with the participants and with the setting in which the programme needed to be carried out. A *linkage board i*s formed, responsible for the execution of the implementation plan. This linkage board consists of the researcher, a care director and a middle manager of the participating ID care provider services. Staff members in the homes of potential participants will be informed about the study and the importance of physical activity for their clients by their manager and researchers.

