**Methods and design:**

The Intervention Mapping protocol was used for programme development. After defining the programme’s objectives, the following behavioural techniques were selected to achieve them: Tailoring, Education, Modelling, Mirroring, Feedback, Reinforcement and Grading. With professionals and managers of provider services for people with intellectual disabilities, we translated these strategies into a structured day-activity programme, that consisted of a physical activity and an education programme. The programme will be executed in five day-activity centres in groups of eight to ten seniors during eight months, whereas seniors in five other centres receive care as usual. The physical activity level, as measured in number of steps a day, will be used as primary outcome measurement. Secondary outcome measurements include motor fitness, cardio respiratory fitness, morphological and metabolic fitness, ADL, functional deterioration and depressive symptoms. Differences in the primary and secondary outcome measures between participants and controls will be analysed using generalized estimation equations, correcting for day-activity center as cluster.

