## Methods and design

This study will evaluate the efficacy of the “Healthy Ageing- Physical Activity Programme (HA-PAP) for seniors with Intellectual Disabilities”. More specifically, physical activity, fitness and health indices will be compared between older adults with mild-moderate intellectual disabilities (ID) who are assigned to the HA-PAP and who will be given usual care. The programme is developed to be executed in day-activity centres of care organisations for people with ID in the Netherlands, in groups of eight to ten seniors. Intervention Mapping (IM) was applied to systematically develop the programme [12]. The efficacy of the programme will be evaluated in a cluster-randomized clinical trial and to minimize contamination, the level of day centres is used as the randomization level.

HA-PAP was approved by the Medical Ethics Committee of the Erasmus University Centre Rotterdam (NL 29573.078.09).

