When looking at the barriers for older adults with ID regarding physical activity, two important overarching barriers became apparent from the literature and were confirmed by managers and movement experts: a lack of social support [13-15] and the need of specific activities [16-19]. A third important barrier, mentioned by managers and movement experts, was the need for professional support. Enjoyment in physical activity in addition, was a recurrent theme in the interviews with seniors with ID themselves. The facilitators they mentioned were also found in studies among younger adults with ID [13-15] and confirmed by movement experts of the ID care provider services. These needs for social support, specific activities, professional support and enjoyment in activities will be elucidated in this paragraph.

Social support is a robust stimulus for physical activity for everyone, but specifically for seniors with ID. They need to be supported in activities themselves, or in the transfer to the activities, and they mostly do not think of the possibility or have the desire to become physically active themselves [13,14]. Staff members in the residential setting however do not always have enough time or are insufficiently aware of the importance of regular physical activity for their clients [14]. Support by family may be limited after parents have died [16]. Aiming at increasing physical activity among the target group therefore means that we have to make sure that staff is motivated and sufficient staff is structurally available.

Managers and movement experts of the ID care provider services underlined that older adults with ID are in need of specific activities adapted to their age and physical limitations. As a result of childhood disabilities and multi morbidity, decline in physical functioning may start at a younger age when compared to seniors with normal intelligence [18]. Physical limitations such as balance and coordination problems, decrease in mobility and muscle strength [20], combined with limited understanding and often limited experiences with physical activities [15] require professional support to create a safe environment and to select appropriate activities for the group concerned. Such professional support can be provided by physical therapists or physical activity instructors, experienced in conducting physical activities with (older) adults with ID.

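### The activity message to home staff is not confined to intervention homes, so the comparator may be more than usual care and the steps-per-day contrast may be biased toward no difference

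*Protocol article*

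**What the plan says.** The last sentence of Forums for implementation reads, in part: "Staff members in the homes of potential participants will be informed about the study and the importance of physical activity for their clients". The message comes from the staff's manager and the researchers. The sentence names no arm, no timing relative to baseline, and no length or content beyond this.

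The expression for the people concerned appears again under Randomization: "The matching procedure was conducted with the data of the potential 237 participants". Selection of day-activity centres and participants shows that these 237 are the clients of all ten centres who met the inclusion criteria, before the centres were split into two sets of five.

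The abstract says that "seniors in five other centres receive care as usual", and Methods and design likewise sets the programme against usual care. Methods and design gives one safeguard: "to minimize contamination, the level of day centres is used as the randomization level". Homes are not mentioned there.

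On home staff, Step 1 of Development of the programme says: "Staff members in the residential setting however do not always have enough time or are insufficiently aware of the importance of regular physical activity". For raising activity it concludes that "we have to make sure that staff is motivated and sufficient staff is structurally available".

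**The concern.** Randomising day centres keeps the programme out of control centres. It does not govern what is said in the homes where clients of both arms live. If control homes are told by managers and researchers that activity matters, the control arm receives something that ordinary care does not include, aimed at a shortfall that the article itself identifies.

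The primary outcome can register a response. It is steps per day from a pedometer worn for at least four days, with no stated limit to day-centre hours, so walking encouraged at home would count.

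At stake is what the trial can claim. A report of the programme against usual care would misname the comparison if control homes had been briefed. A small or null difference would also be hard to read: it could mean a weak programme or a stronger comparator.

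**Working it through.** **Step 1. Does the message reach control homes?** Three points favour that reading.
- The expression in Forums for implementation matches the one that Randomization applies to clients of all ten centres.
- Where the article means the intervention side, it tends to say so. Materials and training limits the education training to staff of the centres running the programme, and Monitoring execution of the programme refers to the five such centres.
- Under Step 6, caregivers in participants' homes complete questionnaires, so control homes must be told about the study. The sentence gives study information and the activity message to one audience.

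This is inference. No sentence says outright that control homes are included.

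**Step 2. Is the message neutral?** Not by the article's own account. Step 1 places residential staff who "are insufficiently aware of the importance of regular physical activity for their clients" under the social-support barrier. Table 1 makes social support a determinant in all three phases. Materials and training lists why activity matters for clients as part of what intervention-centre staff are taught.

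**Step 3. When would the contrast shrink?** Let p be the programme effect, b the briefing effect and o the overlap between them (the part of b that the programme makes redundant). If all homes are briefed:
- intervention mean = μ + p + b − o
- control mean = μ + b
- contrast = p − o

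With o = 0 the contrast is p, and an equal additive response cancels. With o > 0 it is smaller than p. If the target is programme plus briefing against untouched usual care, the target is p + b − o and the contrast falls short of it by b. The article gives no value for b or o.

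**Step 4. Illustration of size.** Inputs from Selection of day-activity centres and participants: SD 2146, difference 1073 (1073/2146 = 0.5), alpha 0.10, power 80%, 60 per group. The article does not say whether alpha is one- or two-sided; two-sided is assumed here.

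Reproducing the plan's figure: n = 2(1.645 + 0.842)² / 0.5² ≈ 49.5, so 50 per group, not 60. One-sided 0.10 gives 37. That mismatch is a separate matter; the stated 60 is used below.

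Power = Φ(Δ / (2146 × √(2/60)) − 1.645), with 2146 × √(2/60) = 391.8. The lost fraction f is assumed. Required n grows by 1/(1 − f)².

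| f (assumed) | Δ (steps/day) | Power, 60 per group | n per group for 80% | 1/(1 − f)² |
|---|---|---|---|---|
| 0 | 1073 | 86.3% | 50 | 1.00 |
| 5% | 1019 | 83.1% | 55 | 1.11 |
| 10% | 966 | 79.4% | 62 | 1.23 |
| 20% | 858 | 70.7% | 78 | 1.56 |
| 30% | 751 | 60.7% | 101 | 2.04 |

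Break-even for 80% power: Δ = (1.645 + 0.842) × 391.8 ≈ 974. The loss is 1073 − 974 = 99 steps/day, and 99/1073 ≈ 9%.

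These figures ignore clustering, so 86% is not this trial's power. With 12 evaluable clients per centre (60/5) and an assumed intracluster correlation of 0.02, the design effect is 1 + 11 × 0.02 = 1.22, and power with no dilution at all is already 79.8%.

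**The case against.** **Intervention-only intent.** The sentence closes a section on implementing the programme, and usage is mixed: the abstract and Analysis set participants against controls. An intervention-only reading is therefore open. This stands as a limit on certainty, but the restriction is not written, and the nearest matching expression covers both arms.

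**The briefing may do little.** The Step 1 sentence names lack of time as well as lack of awareness. The plan's answer was to place activity in the day centre, and Table 2 lists no strategy assigned to home staff. A briefing of unknown length may not move step counts eight months later. If it came before baseline, the baseline adjustment in Analysis could absorb an effect already present by then. All of this is fair, and it is why no size can be assigned.

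**Equal responses cancel.** This is correct, as Step 3 shows. A reader might infer that any response in control homes must shrink the difference, or that the control arm has definitely ceased to be usual care. The documents support neither: shrinkage needs overlap or a different target, and control-home exposure is inferred.

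**Arm-specific briefings have risks.** Allocation preceded consent and is withheld from clients and family until consent ends. Two versions of the briefing before then could reveal it. Home caregivers also complete the mobility, daily-living, depression and deterioration forms. The first risk is met by timing. The second is modest, because participants and/or family are told the allocation after consent anyway, and a neutral briefing in every home removes it.

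What remains is that the text, as written, does not square the message with the stated comparator.

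**Conclusion.** The point holds in conditional form. The article does not confine the activity message to intervention homes, and its own wording points to homes of both arms. By its own reasoning the message acts on something the programme also targets. The comparator may therefore be enhanced usual care, and the steps contrast may be biased toward no difference by an unknown amount.

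That bias needs either overlapping effects or a target of programme against untouched usual care. If responses are equal and additive, the trial still validly estimates the programme on top of briefed homes, but this is not the comparison the article describes.

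The power figures are illustrative: the lost fraction is assumed, alpha is taken as two-sided, and clustering is ignored. They show only that the margin is thin, since a loss of about 99 steps/day (9%) takes power at 60 per arm below 80%. The change is worth making because it costs little and protects the stated comparison.

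**What to change.** Reword the sentence in Forums for implementation so that:
- before and during recruitment, all homes get a neutral briefing only, on study procedures, pedometer wear and questionnaires;
- no home with any control client gets the activity message until the eight-month measurements are complete;
- if the message is used in homes serving intervention clients only, it is given after consent and baseline are complete and is described as part of the programme;
- homes serving clients of both arms are recorded.

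The cost is a revised sentence, two versions of the briefing and a simple record of homes, with no additional participants. Control and mixed homes would get the message about eight months later. Caregivers who complete secondary questionnaires would be briefed differently by arm; keeping the briefing neutral in all homes until follow-up ends avoids this.

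If the sponsor prefers to brief every home, the article should say so, state when this happens relative to baseline, and describe the comparator throughout as usual care plus home-staff information.
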